**Fig. 1 Fig1:**
[figure not shown]
Standard Protocol Items: Recommendations for Interventional Trials (SPIRIT) Figure: the schedule of enrollment, interventions, and assessments

The allocation envelope will be opened by the surgeon when conducting the interference. It will not be possible to mask the treatment allocation from the treating surgeon. Nevertheless, measures will be taken to minimize bias:The patients will not be informed regarding whether they will receive the novel site or the traditional site methodTo minimize detection and selection bias, the exact method of PA will not be documented in the medical recordsThe investigator performing the statistical analyses will be blinded to treatment assignments until the final analysis is completed

### Study participants

Those patients with parathyroid glands that are hard to preserve in situ, or that are mistakenly removed during primary thyroidectomy, will be screened for the inclusion criteria in our study, including malignant and non-malignant disease. Since 10–67% of adults have thyroid nodules on ultrasonography, 10–40% of which were reported as malignant [17, 18], both malignant and non-malignant thyroid diseases were taken into consideration at randomization and analysis. Participants aged from 18 to 65 years old will be enrolled, and those with hyperparathyroidism will be excluded (Fig. 2).

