**Methods:**

In total, 280 patients will be enrolled in this study and randomly divided into two groups: 140 patients with transplanted parathyroid glands in the traditional sites (group A) and the other 140 transplanted in the novel sites (group B), close to the antecubital veins. The serum concentration of PTH and calcium ion from both forearms will be measured and monitored regularly for 12 months. The primary outcome of this trial will be the survival of grafted glands, defined as the ratio of PTH between the grafted vs. the non-grafted forearms being no less than 1.5. The secondary outcome is hypoparathyroidism, defined as the PTH level from the non-grafted forearms being less than 15 pg/ml (normal range 15–65 pg/ml).

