## Methods

### Study design

This is a prospective, randomized controlled trial to apply PA at the novel sites and to assess the survival rate of transplanted parathyroid glands in thyroidectomy patients. A 1:1 block randomization will be performed at the same clinical center and operations will be carried out by the same experienced surgeon in Tongji Hospital (Wuhan, China). The study has been approved by the Ethics Committee of Tongji Hospital, Tongji Medical College, Huazhong University of Technology Institutional Review Board with approval given on 25 June 2015 (reference number: TJ-C2015602) (Additional file 1).

In this single-center study, hospitalized patients with primary thyroidectomy in Tongji Hospital will be enrolled. Stochastic indicators were used to generate the random allocation sequence of the patients. Sequentially numbered containers were employed to implement the random allocation sequence and to conceal the sequence until interventions are assigned for implementation. Analysts in our study generated the random allocation sequence while care providers numbered the qualified participants. The surgeon assigned participants to interventions based on the condition of their parathyroid glands during thyroidectomy. All subjects, researchers in the laboratory and data analysts will be blind to the group classification.

Primary endpoint: the ratio of the serum PTH level from the grafted vs. the non-grafted forearm level is no less than 1.5 and the percentages of the 1.5 ratio in the experimental group are obviously higher than those in the control group. Since successful PA was defined as the ratio of the PTH level from the grafted to the non-grafted forearms as not less than 1.5, we set the primary endpoint in line with expert opinion, and the percentages of no less than the 1.5 ratio in the experimental group are obviously higher than those in the control group. 

Secondary endpoints: serum PTH less than 15 pg/ml, and lasting for more than 6 months, as well as a low serum calcium level requiring oral supplements to be taken. Duration of hospital stay will be documented according to hospital charts. During the 1-month to 12-month follow-ups after surgery, patients will be interviewed to assess for postoperative hypocalcemia.

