### Sample size calculations

The experimental group involves the participants with PA at the novel sites closer to the cephalic vein, while the participants in the control group generally receive subcutaneous transplantion. Since the survival rate of the traditional assessing method was reported as 45% [16], and that of the new method was predicted as 65% in our preliminary study (unpublished data). We set α as 0.05 (bilateral), power as 0.90 and obtained the sample size *N*1 = *N*2 = 128 by PASS 11. To compensate for a loss to follow-up, we set the final sample size as 280 in all.

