### Data management and statistical analysis

One of the researchers, who is an expert in statistics and blind to treatment assignments, will perform the analysis. The sign that a PA has survived will be set as the higher PTH ratio between the grafted and non-grafted forearm, which will be analyzed by a *Χ*^2^ test. All parameters will be analyzed by appropriate statistics with SPSS 22.0, including categorical data and normally distributed numerical data. The former will be compared using a *Χ*^2^ test or Fisher’s exact test and the latter will be analyzed by a *t* test and the Mann-Whitney *U* test if skewed. A Cox model will be used to verify the factors affecting PA survival. Data will be collected in the CRF and consent forms are preserved in a locked computer kept in a locked room. Each participant will be identified by randomization number to ensure the confidentiality of this study.

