### Subgroup analysis

We will compare the primary outcome between subgroups characterised by: (1) high vs. low adherence; (2) malignant vs. non-malignant thyroid disease; (3) age categories (18–45, 46+ years); (4) gender and Body Mass Index (BMI) categories (< 25, 25+ kg/m^2^); and (5) parathyroid numbers autotransplanted and preserved.

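### Malignancy is said to enter randomization and analysis, but no strata are named and the primary chi-square is unstratified; a stratified primary test would be a low-severity, nearly free improvement

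*Protocol article*

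**What the plan says.** Under Study participants, the protocol article gives background figures on thyroid nodules and then states that "both malignant and non-malignant thyroid diseases were taken into consideration at randomization and analysis". It does not say how.

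Three other places bear on this:

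- Study design: "A 1:1 block randomization will be performed at the same clinical center". No stratification factor is named.
- Data management and statistical analysis: the indicator of graft survival is the forearm PTH ratio, "which will be analyzed by a *Χ*^2^ test". No stratum or covariate is named. The section adds that "A Cox model will be used to verify the factors affecting PA survival", without listing the factors.
- Subgroup analysis: the primary outcome will be compared by "2) malignant vs. non-malignant thyroid disease", among other factors.

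The abstract makes the primary outcome binary: graft survival is "defined as the ratio of PTH between the grafted vs. the non-grafted forearms being no less than 1.5".

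**The concern.** If a factor is used to balance the allocation, the primary analysis should normally reflect it. Otherwise the test uses a variance that includes between-stratum differences which the design has already removed, and it becomes conservative. If the factor was not used in the allocation, the sentence under Study participants is wrong about randomization, and chance imbalance on the one disease characteristic the authors single out stays in the primary comparison.

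The article supports neither case clearly. What is at stake is some precision, the reader's ability to know how patients were allocated, and a choice between adjusted and unadjusted results that could still be made after the data are seen.

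**Working it through.** **1. The planned sample size.** Inputs from Sample size calculations: 45% against 65%, two-sided α 0.05, power 0.90. The pooled-variance formula without continuity correction is

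n = [1.96·√(2·p̄·q̄) + 1.2816·√(p₁q₁ + p₂q₂)]² / (p₂ − p₁)²

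with p̄ = 0.55:

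- 1.96·√0.495 = 1.379
- 1.2816·√0.475 = 0.883
- n = (2.262)² / 0.04 = 127.9, so 128 per arm

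This matches the stated figure. The 90% power is therefore that of an unstratified two-proportion test and does not depend on malignancy. With 140 per arm it is 0.924.

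**2. Why the plain test is conservative under stratified blocks.** With equal strata exactly balanced between arms, let r be the within-stratum variance divided by the total variance. The plain standard error is then too large by a factor 1/√r, and the true size is 2·[1 − Φ(1.96/√r)]. Illustrative stratum rates averaging 45%, so total variance 0.45·0.55 = 0.2475:

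| Rates | Odds ratio | r | Standard error too large by | True size |
|---|---|---|---|---|
| 35% / 55% | 2.3 | 0.2375/0.2475 = 0.960 | 2% | 4.5% |
| 30% / 60% | 3.5 | 0.2250/0.2475 = 0.909 | 5% | 4.0% |
| 25% / 65% | 5.6 | 0.2075/0.2475 = 0.838 | 9% | 3.2% |

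**3. Simulation at the planned size.** Settings: 128 per arm, marginal rates held at 45% and 65%, 60,000 runs per setting, plain chi-square against a Mantel-Haenszel test stratified by malignancy. The malignant share was varied from 10% to 90% and the odds ratio of malignancy for the outcome from 1 to 5. Both are assumptions: the article gives only a background figure (10-40% of nodules) and no prognostic effect. Results at a 50% share:

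| Odds ratio | Stratified blocks: power, plain / stratified test | Type I error, plain test | Standard error, stratified / plain | Unstratified blocks: power, plain / stratified test |
|---|---|---|---|---|
| 1 | 0.904 / 0.904 | 0.0528 | 0.996 | 0.904 / 0.902 |
| 1.5 | 0.903 / 0.903 | 0.0507 | 0.991 | 0.901 / 0.902 |
| 2 | 0.907 / 0.908 | 0.0473 | 0.982 | 0.900 / 0.904 |
| 3 | 0.908 / 0.916 | 0.0445 | 0.961 | 0.903 / 0.918 |
| 5 | 0.917 / 0.937 | 0.0354 | 0.925 | 0.902 / 0.936 |

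A share of 50% is close to the worst case; at 10% or 90% the differences are smaller. Inverting the standard-error ratios gives about 1-2% too large at odds ratios 1.5-2, 4% at 3 and 8% at 5 (1/0.925 = 1.08). About 0.4% of each figure comes from the variance formulas, since the ratio is 0.996 with no effect at all.

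Under unstratified blocks the plain test keeps a size of about 0.05 and power of about 0.90. The stratified test still gains there, because it removes chance imbalance: nothing at odds ratio 1, and 0.936 − 0.902 = 3.4 points at 5.

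**The case against.** The best defence is that the sentence under Study participants never says stratified. It follows a statement that both disease types are eligible, and its stated reason is prevalence, not prognosis. It could mean only that both kinds of patient are enrolled, randomized and analysed. Silence on strata under Study design is not a statement that there were none, and a condensed article may leave such detail to the full protocol. The subgroup analysis, and perhaps the Cox model, could be what is meant by considering malignancy in the analysis.

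Much of this stands. Stratified blocks are not established, and malignancy is not wholly absent from the analysis. The sentence nevertheless makes a claim about randomization that nothing else in the article explains. A subgroup comparison does not bring malignancy into the primary test, and the Cox model is described as a search for factors affecting survival, not as the comparison of arms.

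A reader might infer three stronger things that the article does not support:

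- **The trial is underpowered.** It is not on this account, because 128 per arm was derived for the unstratified test. In the 30% / 60% illustration a stratified test could reach the same power with about 9% fewer patients (0.09 × 128 ≈ 12 per arm). That is a possible saving under invented inputs, not a shortfall.
- **The planned confidence interval is too wide.** The article plans no confidence interval for the primary comparison.
- **The plain chi-square is invalid.** With unstratified blocks it has about its nominal size. With stratified blocks any departure is conservative, so a positive result is not threatened.

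**Conclusion.** The inconsistency is real and minor. The article claims that malignancy was considered at randomization and analysis, but describes neither a stratified allocation nor a primary test that uses malignancy.

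The size of the effect rests on two undocumented conditions, stratified blocks and a prognostic effect of malignancy. If both hold, the power forgone is at most about 0.1 point for odds ratios up to 2, under 1 point at 3 and about 2 points at 5. With no prognostic effect nothing is lost. If blocks were not stratified, the plain test is valid, and stratifying the analysis is a choice that corrects chance imbalance. Low severity; a free improvement.

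**What to change.** 1. State truthfully under Study design whether the blocks were stratified by malignant and non-malignant disease. If they were not, correct the sentence under Study participants. Stratification should not be written in after the fact: Trial status gives an April 2016 start and describes recruitment as under way, so the statement could be false.
2. Before unblinding, name as primary test a Cochran-Mantel-Haenszel test stratified by the preoperative diagnosis (malignant or non-malignant), or a logistic regression with that diagnosis as covariate. If blocks were stratified, use the diagnosis as classified at allocation.
3. Report the stratified risk difference with its 95% CI. With dₖ the arm difference in stratum k and weights wₖ = n₁ₖn₀ₖ/(n₁ₖ + n₀ₖ), this is Σwₖdₖ/Σwₖ.
4. Keep the plain chi-square as a sensitivity analysis. If treatment codes have already been opened, leave it as primary and report the stratified result as the sensitivity analysis.

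The cost is a few sentences and a dated amendment. Diagnosis is already listed among the preoperative variables, so no new data or patients are needed, and the sample size need not change.

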**Fig. 2 Fig2:**
[figure not shown]
Study flowchart

### Sample size calculations

The experimental group involves the participants with PA at the novel sites closer to the cephalic vein, while the participants in the control group generally receive subcutaneous transplantion. Since the survival rate of the traditional assessing method was reported as 45% [16], and that of the new method was predicted as 65% in our preliminary study (unpublished data). We set α as 0.05 (bilateral), power as 0.90 and obtained the sample size *N*1 = *N*2 = 128 by PASS 11. To compensate for a loss to follow-up, we set the final sample size as 280 in all.

### Informed consent

Informed consent will be obtained from all participants in the study prior to surgery and confirmation will be made after PA. If the patient is unable to give consent, it will be sought from a close relative. Withdrawal from the study is possible at any time, in accordance with the latest version of the Declaration of Helsinki 2013.

### PA protocol

Patients will undergo operations in the supine position under general anesthesia. The removed parathyroid glands will be placed in sterile physiological salt solution at 4 °C until confirmed by the frozen-section diagnoses. The parathyroid glands will be sliced into 2–4-mm cubes and mixed with 0.5 cc sterile physiological salt solution in a 1-cc syringe. The parathyroid fragments will be subcutaneously injected into the non-dominant forearm with a 16-G needle [19].

The novel site method means choosing the graft site close to the antecubital veins, including the cephalic vein, the median cubital vein and the basilic vein. During the follow-up, blood samples will be taken from the vein near the graft site (Fig. 3), as well as from the opposite forearm. The traditional site method means general transplantation further away from the relevant antecubital veins. In Fig. 3, the novel sites are points A and B and the traditional are points C and D. All of the grafted forearms from the two groups will be pressed gently immediately after transplantation. The blood samples will be taken at five different time points: 3 days, 1 month, 3 months, 6 months and 12 months after transplantation.

**Fig. 3 Fig3:**
[figure not shown]
The novel site of parathyroid autotransplantation (PA). In the forearm, the novel site was chosen close to the cephalic vein (point A or B), which is convenient to obtain blood samples. The traditional site is chosen to be more distant to the cephalic vein, such as points C and D

### Baseline variables

Variables will be documented in the Case Report Form (CRF) preoperatively, intraoperatively and within 72 h postoperatively by the attending surgeon.

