#### Postoperative variables

PTH assays taken from the grafted and non-grafted forearms, serum calcium ion and phosphate levels, symptoms of limb numb or twitch, wound healing of the transplantation site, and duration of postoperative drainage.

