### Outcome measures

Basal concentrations of PTH from both arms and the concentration of serum calcium will be obtained before and after surgery. Postoperative evaluation of symptoms and signs of hypocalcemia will be recorded as well as oral supplements with calcium and calcitriol. Two researchers will be assigned to record the examination results of participants, and to take blood samples.

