### Follow-up

The follow-up period is 12 months. In order to strengthen the monitoring adherence, most patients will be contacted through WeChat, QQ chat, mobile phones, emails and the regular outpatient interview. Follow-up will be scheduled on the third day and the first, third, sixth and 12th months postoperatively.

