## Limitations

Although the surgeon could not be blind to the participants’ information, the follow-up information and data analyses will be performed by the researchers blind to the exact PA method. The follow-up of 12 months is also a limitation of the research in postoperative hypoparathyroidism. Besides, the surgical strategy is so homogeneous that subtle differences in the surgical method cannot be excluded. Furthermore, as this novel system is only applied to evaluate PA survival level, the relative factors required for improving PA survival rate will be conducted in the subsequent investigation.

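### The apparently unmasked surgeon records symptoms and graft-site healing up to 72 h, and the researchers who record later results also draw blood beside the graft, so the claimed blinded follow-up is not secured

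*Protocol article*

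**What the plan says.** All statements are in the protocol article.

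- **Baseline variables:** CRF entries are made before surgery, during surgery and "within 72 h postoperatively by the attending surgeon". Three sub-lists follow. The third, Postoperative variables, holds PTH from both forearms, calcium and phosphate, "symptoms of limb numb or twitch", healing at the graft site, and drainage duration.
- **Study design:** one surgeon performs all operations. After Fig. 1: "The allocation envelope will be opened by the surgeon when conducting the interference", and "It will not be possible to mask the treatment allocation from the treating surgeon". Those listed as blind to group are the subjects, the laboratory researchers and the data analysts.
- **Follow-up:** "Follow-up will be scheduled on the third day", then at months 1, 3, 6 and 12. The PA protocol section sets blood samples at the same five times, the graft-side sample coming from a vein close to the graft.
- **Outcome measures:** symptoms and signs of hypocalcemia and oral supplements are to be recorded. "Two researchers will be assigned to record the examination results of participants, and to take blood samples".
- **Limitations:** in answer to the surgeon's lack of masking, "the follow-up information and data analyses will be performed by the researchers blind to the exact PA method".

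**The concern.** For the day-3 visit the article names two different recorders. One of them appears to be the person who opened the envelope and placed the graft. Limitations relies on blinded follow-up to offset exactly that person's knowledge of the arm, so the safeguard is in doubt at the first visit.

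A second weakness does not depend on the surgeon. The randomized difference is how close the graft lies to the antecubital veins. Anyone who must find the graft in order to sample the vein beside it may be able to tell the arm. The same two people are assigned to record results.

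At stake are the outcomes that need judgement: symptoms and signs of hypocalcemia, and wound healing. A recorder who knows or guesses the arm can influence these without intending to. The text after Fig. 1 names detection bias as something the trial means to minimize.

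**Working it through.** No figure in the plan bears on this point. The sample size (128 per group before allowance for loss, 280 in total) rests on the proportion with graft survival and is not affected. The check is a comparison of statements, with one piece of arithmetic.

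1. **Timing.** Day 3 = 3 × 24 h = 72 h. The surgeon's recording window and the first follow-up visit meet at the window's edge.
2. **Does the window reach outcome data, or only baseline data?** The heading says baseline, but the postoperative list stands under it and includes PTH from the grafted forearm. That value exists only after transplantation, and the first post-transplant sample in the schedule is on day 3. The window therefore reaches the day-3 data.
3. **Who is the attending surgeon?** The article does not say outright that this is the operator. It describes only one surgeon, who performs every operation, so the identification is likely but inferred.
4. **Who records on day 3?** Baseline variables gives the surgeon; Outcome measures gives two researchers; Limitations gives blinded researchers. If the surgeon makes the day-3 entries for symptoms and wound healing, the Limitations statement is untrue for that visit. If the researchers make them, the Baseline variables statement is wrong.
5. **Are the two researchers blinded?** Outcome measures does not say so, and the list of blinded parties in Study design does not name outcome recorders or blood drawers. Limitations claims it.
6. **Can that claim hold while they draw blood?** The sentence on sampling near the graft sits between the definitions of the novel and the traditional site. If it applies to both arms, the drawer must locate the graft. If it applies only to the novel arm, the drawer must know the arm. Either way the claim is weak, at all five visits.
7. **Which outcomes are exposed?**
   - PTH ratio of at least 1.5 (primary): a laboratory value, with laboratory staff blinded. Not exposed in this way.
   - PTH below 15 pg/ml for more than 6 months (secondary): also a laboratory value, and not decided at day 3.
   - Symptoms and signs of hypocalcemia: judged. Exposed at day 3 through the surgeon, and at every visit through the combined recording and sampling role.
   - Graft-site healing: judged, and cannot be assessed without seeing the site.
   - Supplements: not in the postoperative list under the surgeon's window, so not assigned to the surgeon. They appear under Outcome measures and fall under the second issue only.

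**The case against.** The strongest reply is that no conclusion of the trial rests on the disputed day-3 entries. The primary outcome is a laboratory ratio, the PTH secondary endpoint needs more than 6 months, and Study design places the hypocalcemia interviews at months 1 to 12. This stands, and it limits the point. A reader might infer that the primary comparison is compromised; the documents do not support that.

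A reader might also want to put a false-positive rate on the bias by supposing a shift in day-3 symptom rates. The article gives no symptom rate and states no between-arm test of day-3 symptoms, so any such figure would rest on invented inputs and describe an unplanned test.

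It can also be said that the surgeon documents perioperative variables while the researchers record outcome examinations. That division would work, but the article does not state it, and the postoperative list under the surgeon's window contains outcome items. The overlap is at the 72 h boundary only; months 1 to 12 are not assigned to the surgeon.

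Finally, it would go too far to say that blinding is absent at day 3. Patients are not told their site, and numbness is something the patient reports. Laboratory staff and analysts remain blinded, the exact method is kept out of the medical records, and the article openly discloses that the surgeon is unmasked. Nor is the surgeon the only person who could know the arm, since those drawing blood may infer it. What remains is that the recorder's blinding is claimed but not secured.

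**Conclusion.** The point holds in limited form. The article contradicts itself on who records the day-3 symptoms and graft-site healing and whether that person is blinded: one of five visits, in all 280 planned patients. Separately, combining result recording with blood sampling near the graft weakens the blinding claim at all five visits.

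The exposure is confined to judged outcomes. The laboratory PTH ratio, the sample size and the planned error rates are unaffected, and the size of any bias cannot be derived from the documents. The first part assumes that the attending surgeon is the operator and that day 3 falls within the 72 h window. The second assumes that finding the graft can reveal the arm. It is worth correcting because symptoms and signs of hypocalcemia are listed outcome measures and the remedy is cheap.

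**What to change.** - **Baseline variables:** limit the surgeon's CRF entries to preoperative and intraoperative variables, plus objective early postoperative items such as drainage.
- **Outcome measures:** have one of the two named researchers draw blood. Have the other, who does not see the graft site, record symptoms and supplements at every visit, including any symptom entries before day 3, so that no period lacks a recorder.
- **Wound healing:** report it as an unblinded assessment.
- **Limitations:** correct the text to say who records what, and who is blinded.

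The cost is a change of wording and of CRF responsibility, with no extra staff and no change to the sample size. The small downside is that the two researchers' tasks must be scheduled separately. The study began in April 2016, so for visits already completed only the last two changes remain open: disclose who recorded the judged outcomes and whether they could have known the arm.
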